To ensure data quality and reproducibility, EEG signals will undergo standardized pre-processing procedures. Data will be processed in MATLAB R2025a (MathWorks, Natick, MA, USA) using EEGLAB v2025. Continuous recordings will be visually inspected to identify gross artifacts or recording instabilities, and non-EEG channels will be removed prior to analysis. Signals will be band-pass filtered between 1 and 45 Hz using a zero-phase finite impulse response (FIR) filter and re-referenced to a common average reference. Artifact correction will be performed using Independent Component Analysis (extended infomax algorithm). Independent components will be automatically classified using the ICLabel plugin integrated in EEGLAB, and components identified as ocular, muscular, cardiac, line-noise, or other non-brain sources with high probability (≥0.90) will be removed prior to signal reconstruction. Channels exhibiting persistent excessive noise throughout the recording will be excluded from analysis. All preprocessing procedures will be applied consistently across participants and experimental conditions to ensure methodological standardization and internal validity.

Oculomotor activity will be recorded with the Pupil Core system (Pupil Labs GmbH, Germany), with sampling at 200 Hz. This equipment will allow the analysis of fixations, saccades, pupillary dilation or and blink rate, during the LSPT. The ETS was only applied in the LSPT, as it contains visual stimuli while performing gaze orientation and control of attention, appearing as especially appropriate to analyze gaze patterns (53). In addition, the LSPT is longer in duration, which makes it possible to collect consistent eye activity data. Vansteenkiste et al. (54) demonstrated a correlation between LSPT performance and gaze patterns in young players, reinforcing that this type of test is suitable for analyzing oculomotor metrics. In contrast, the Y-SART is a simple task and it presents brief visual stimuli, so the use of an eye-tracker is not justified. Recent research has demonstrated that motor skills (e.g., sprinting, changing direction, reactive strength) are the main determinant in performance on the Y-SART and is also affected by sensory/perceptual processes to a smaller extent or indirectly (55). The data will be processed with open-source software provided by the manufacturer.

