### Performance assessment

2.4

After collecting baseline data, participants will perform two motor tests as part of Phase 3 of the protocol. The first is the LSPT, which assesses passing accuracy and speed under time pressure in a standardized soccer-specific context. Participants perform 16 passes to designated targets announced in sequence, with performance assessed by total execution time adjusted for penalty points for technical errors (e.g., incorrect passes, errors in the target area, poor ball handling) and bonus points for accurate actions. This scoring protocol has been validated in youth and elite football players (56, 57). The test will be filmed with two cameras for subsequent technical analysis and penalty verification. A schematic representation of the LSPT setup is provided in Figure 2, adapted from Ali et al. (34).

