**Figure 3 F3:**
[figure not shown]
Schematic representation of the Y-SART, adapted from Yuan et al. (2).

After completing Phase 3, participants move on to Phase 4, where they perform the cognitive intervention defined by their group assignment, either the ST (experimental group) or a neutral task, such as reading magazines (control group). This is followed by Phase 5, which begins with participants completing the VAS again. Next, both motor tests are repeated, this time with continuous recording by the ETS. Finally, a second EEG recording is performed under the same conditions as in the initial phase, concluding the data collection session.

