#### Oculomotor parameters (ETS)

2.5.2

Oculomotor parameters will be monitored using the Pupil Pro Eye Tracking Headset (Pupil Labs GmbH, Germany) to assess neurophysiological changes associated with mental fatigue induced by the ST. The metrics analysed will include the number and average duration of fixations, the duration and average speed of saccades, pupil diameter, and blink rate, parameters widely recognized as sensitive indicators of cognitive load, attention regulation, and fatigue-related decline in vigilance (69–72). To minimize potential confounding influences, standardized task instructions, calibration procedures, controlled lighting conditions, and consistent testing environments will be implemented. Moreover, the within-subject pre-post design allows each participant to serve as their own control, thereby reducing the impact of inter-individual variability in visual strategies and perceptual tendencies.

In addition to descriptive characterisation, the study will include comparisons between the experimental and control groups in terms of these oculomotor parameters after the intervention phase. These comparisons will assess whether mental fatigue induced by the ST produces significant changes in visual-attentional dynamics compared to a cognitively neutral task. Specific attention will be given to variations in blink rate, pupil diameter, fixation duration, and saccade characteristics.

Within the experimental group, oculomotor parameters will be compared before and after the intervention to identify the direct impact of cognitive overload on visual attention and eye movement control. This intragroup analysis is crucial for understanding the dynamic response of the oculomotor system to cognitive stress.

In addition, correlational analyses will be performed between ETS data and behavioral performance on the LSPT and Y-SART to explore whether visual-attentional indicators predict motor performance under fatigue. A multimodal approach will also be employed to assess convergence between different markers of fatigue (ETS, EEG, and VAS), providing a comprehensive understanding of how different modalities reflect fatigue-related changes.

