For EEG data (theta, alpha, and beta bands), spectral power within predefined regions of interest (ROIs) will be analyzed using repeated-measures models including Time (pre vs. post mental fatigue) and Recording Condition (eyes open, eyes closed, motor imagery), allowing evaluation of fatigue-related changes across neural states. Primary analyses will focus on frontal midline and posterior ROIs, consistent with the study's theoretical hypotheses. Exploratory analyses across additional scalp regions will be conducted separately and corrected using False Discovery Rate (FDR) procedures to control for multiple comparisons. Correlational analyses (Pearson's r) will explore associations between EEG bands and behavioral performance (LSPT, Y-SART), as well as subjective fatigue scores (VAS and FAS) (94, 95). Topographic maps will be generated to visualize EEG power distributions across cortical regions.

For oculomotor parameters (fixations, saccades, pupil diameter, blink rate), comparisons will assess the impact of mental fatigue on attention dynamics and visual search efficiency. Pearson correlations will explore links between ETS metrics, EEG patterns, and motor performance scores. Eye-tracking outcomes will be interpreted in conjunction with EEG measures, motor performance variables, and subjective fatigue scores, allowing a multimodal framework that reduces interpretative ambiguity.

Motor performance will be analyzed by comparing LSPT and Y-SART results before and after cognitive induction. Metrics such as execution time, technical penalties, and reaction times will be examined to determine whether cognitive fatigue impairs decision-making and technical execution under pressure.

These performance results will be correlated with neurophysiological and oculomotor indicators to investigate predictive relationships. Subjective fatigue will be analyzed using pre and post VAS comparisons and baseline FAS scores. These will be used to triangulate subjective perceptions with objective changes in EEG, ETS, and performance data. Higher self-reported fatigue scores are expected to align with reduced cortical efficiency, altered visual behavior, and degraded motor output.

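### Gaze and the LSPT score come from the same run, so their correlation is concurrent and cannot show that gaze predicts passing performance

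*Protocol article*

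**What the plan says.** All references are to the protocol article.

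- **Where gaze is recorded.** Section 2.3 (Mental fatigue assessment): "This equipment will allow the analysis of fixations, saccades, pupillary dilation or and blink rate, during the LSPT", and "The ETS was only applied in the LSPT". No separate gaze task is described.
- **How the LSPT is scored.** Section 2.4 (Performance assessment): "performance assessed by total execution time adjusted for penalty points for technical errors", with bonus points as well. Section 2.5.3.1 lists total execution time, technical penalties and adjusted score as the variables to be analysed.
- **Which gaze metrics.** Section 2.5.2 (Oculomotor parameters) includes "the number and average duration of fixations", together with saccade duration and speed, pupil diameter and blink rate.
- **What the correlation is for.** Section 2.5.2 relates eye-tracking data to LSPT and Y-SART performance "to explore whether visual-attentional indicators predict motor performance under fatigue". Section 2.6 (Statistical analysis) names the method, "Pearson correlations will explore links between ETS metrics, EEG patterns, and motor performance scores", and states the purpose: "These performance results will be correlated with neurophysiological and oculomotor indicators to investigate predictive relationships".
- **Stated safeguard.** Section 2.6 says that gaze will be interpreted jointly with EEG, motor and subjective measures. Section 2.5.2 adds calibration, lighting, standard instructions and the pre-post design.
- **A conflict on the tracker.** Section 2.4, on Phase 5, says that "both motor tests are repeated, this time with continuous recording by the ETS". This disagrees with the LSPT-only statement in section 2.3. It can also be read as meaning that gaze is not recorded at baseline, although section 2.5.2 plans a before-after comparison of gaze.

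**The concern.** Prediction needs the predictor to come before the outcome, or at least not to be produced by it. Here both are summaries of one run of 16 passes. An incorrect pass or poor ball handling worsens the score. If the player then has to follow or recover the ball, it also lengthens the run and changes what the eyes are doing while the tracker records. Causation can run from gaze to errors, from errors to gaze, or both ways, and a Pearson coefficient is the same in each case.

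Two things are at stake. A correlation produced by errors or run length could be reported as a visual-attention predictor of technical performance and carried into the regression-based fatigue profiles of section 2.6. Also, if the Stroop arm makes more errors, as section 2.5.3.1 leads one to expect, part of any gaze difference between arms could be time spent on errors and be read as less efficient visual search.

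**Working it through.** **Sample size used below.** The article states 34 players for f = 0.25, alpha 0.05 and 80% power. With the usual repeated-measures formula and an assumed pre-post correlation of 0.5, λ = f²·N·m/(1 − ρ) = 0.0625 × 34 × 2 / 0.5 = 8.5 on 1 and 32 df. Power is 0.807, so the figure reproduces. The argument does not depend on it; N = 34 only sets the critical correlation. Two-sided at 5%, that is t/√(n − 2 + t²) = 2.037/√(32 + 4.149) = 0.339 for n = 34, and 0.482 for one arm of 17. Table 1 gives 24 men and 24 women, so n = 48 is shown as well.

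The article gives no variances, error rates or recovery times. **Every input in steps 1 to 3 is an assumption, and gaze has no effect on performance in any of them.**

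**Step 1. Fixation count against execution time.** Count = rate × time. If rate and time are independent with coefficients of variation c_R and c_T,

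r = c_T / √(c_T² + c_R² + c_T²·c_R²).

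- c_T = 0.08, c_R = 0.30: 0.08/0.311 = 0.26
- c_T = 0.12, c_R = 0.20: 0.12/0.234 = 0.51
- c_T = 0.18, c_R = 0.10: 0.18/0.207 = 0.87

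Simulation over this grid (20,000 replicates per setting) gives mean r of 0.25 to 0.87. The 5% test rejects in 32% to 100% of trials at n = 34, 17% to 100% at n = 17 and 43% to 100% at n = 48.

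**Step 2. Run-mean fixation duration against errors.** Assume:

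- 16 passes of 2.5 s, giving 40 s of passing;
- errors on 30% of passes, between-player SD 12 points;
- recovery time τ of 1.5 to 3 s per error;
- recovery fixations longer or shorter than passing fixations by a fraction δ (20-30% shorter or 15-50% longer);
- between-player SD of fixation duration 8% to 12%.

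The number of errors k has mean 16 × 0.3 = 4.8 and variance 16 × 0.21 + 16 × 15 × 0.0144 = 6.82, so SD 2.61. With passing fixation duration d, the run mean is d(40 + kτ)/(40 + kτ/(1 + δ)). Its proportional change per error, near k = 4.8, is

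τ/(40 + 4.8τ) − [τ/(1 + δ)]/(40 + 4.8τ/(1 + δ)).

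- Weak corner (τ = 1.5, δ = +0.15, SD 12%): 0.0318 − 0.0282 = 0.0036 per error; × 2.61 = 0.0094; r ≈ 0.0094/√(0.0094² + 0.12²) = 0.08.
- Strong corner (τ = 3, δ = −0.30, SD 8%): 0.0551 − 0.0708 = −0.0156 per error; × 2.61 = −0.0408; |r| ≈ 0.0408/√(0.0408² + 0.08²) = 0.45.
- δ = 0: the two terms cancel and r = 0.

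Simulation at n = 34 (4,000 trials per setting) agrees: mean |r| is about 0.08 to 0.45 with rejection in about 7% to 79% of trials, and rejection is 5% when δ = 0.

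**Step 3. The same settings with δ = 0, for the count.** Run time is 40 + kτ, so c_T is 2.61 × 1.5/47.2 = 0.083 at τ = 1.5 and 2.61 × 3/54.4 = 0.144 at τ = 3. With c_R of 0.08 to 0.12, count against run time gives r of 0.56 to 0.87 and rejection in 95% to 100% of trials. Dividing the count by run time brings rejection back to 5%. If δ is not zero, the rate keeps the coupling of step 2.

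**Step 4. Arm comparison.** Under the model in step 2, an error difference of D standard deviations between arms carries about |r| × D into mean fixation duration. The planning effect f = 0.25 corresponds to D = 2f = 0.5 for two groups, so the carry-over is 0.5 × 0.08 = 0.04 to 0.5 × 0.45 = 0.23 SD. A t-test of 17 against 17 would detect this in about 5% to 10% of trials, against 5% with no carry-over.

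**The case against.** The strongest reply has four parts.

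- **The gaze windows may be defined elsewhere.** An article commonly leaves segmentation to the full protocol. This stands: the absence of a window is not itself the fault. The fault is the stated predictive reading of same-run data. A window would reduce the contamination, but the wording would still need to change.
- **The wording is hedged.** The text speaks of exploring links, and prediction can be meant in the ordinary regression sense. This limits the weight of the point, since these are exploratory correlations and section 2.5.1.2 reserves *primary* for EEG analyses. It does not remove it, because two sections give prediction as the purpose. Joint interpretation with other modalities cannot settle direction.
- **Recovery is not described.** Section 2.4 lists the penalised errors but not what the player does next, how long it takes or how gaze behaves. This stands, and it is why step 2 is only an illustration: even its sign is open and the upper end is a corner case. The count-time link needs no difference in gaze during recovery.
- **The quoted sentence also covers EEG.** This stands too. EEG is recorded apart from the motor tests, so same-run coupling does not arise there.

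A reader might infer that the arm comparison of gaze is biased. The documents do not support that. If the Stroop task raises errors and errors alter gaze, the difference is still an effect of the randomised assignment; only its explanation as visual attention is open. A reader might also infer that any gaze-LSPT correlation found will be an artefact. That does not follow either: its direction cannot be identified, which is a weaker statement.

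**Conclusion.** The point holds in a limited form. Gaze metrics and the LSPT result are concurrent measurements from one run, and the article reads their correlation as prediction, which the design cannot support. The coupling is mechanical for number of fixations against total execution time: r of 0.25 to 0.87 over the assumed coefficients of variation, without any influence of gaze. For average metrics the size is unknown. Assumed inputs give |r| of 0.08 to 0.45, and nothing if gaze during recovery equals gaze during passing.

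What is affected is the exploratory gaze-LSPT correlations and the interpretation of gaze differences between arms. The randomised contrast stands as a total effect. LSPT-recorded gaze set against the Y-SART does not share a run. Its time order is right provided that Phase 5 repeats the Phase 3 order, LSPT first, which the text does not restate.

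**What to change.** 1. **Reconcile first.** Sections 2.3 and 2.4 should agree on whether the eye tracker is worn in the LSPT only or in both tests, and on whether gaze is recorded at baseline. Confirm the test order in Phase 5.
2. **Wording.** In 2.5.2 and 2.6, call gaze-LSPT associations concurrent and drop *predict* and *predictive* for them. Keep those words at most for LSPT-recorded gaze against the later Y-SART.
3. **Metric.** Analyse the number of fixations as a rate per unit of run time.
4. **Sensitivity analysis.** For fixation, saccade and pupil metrics, recompute the values from the intervals before each ball strike, leaving out error recovery, and report them beside the whole-run values.

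**Cost.** Items 2 and 3 change only text and one derived variable. Item 4 needs marking of 16 passes per recorded run, on video already taken to verify penalties, and alignment of the camera and eye-tracker clocks. It also leaves less gaze time per player. With windows of 1 to 1.5 s (an assumption), 16 passes give 16 to 24 s. At the 5 to 15 blinks per minute that section 2.5.2.4 gives for demanding tasks, that is 16/60 × 5 = 1.3 to 24/60 × 15 = 6 blinks per run. This is too few for blink rate, which should stay a whole-run measure, and it is why the windowed analysis should not replace the main one.

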## Discussion

3

Although the multimodal approach proposed in this protocol is relatively unexplored in sports science, emerging literature increasingly recognizes the detrimental effects of mental fatigue on attention regulation, decision-making processes, and motor performance, especially in tasks that require cognitive control and rapid perceptual-motor adjustments. Mental fatigue has been associated with increased perceived exertion, decreased motivation, and poorer cognitive control, ultimately leading to a decline in performance in both endurance sports and intermittent disciplines such as football (1, 7). These impairments are believed to stem more from central mechanisms than from peripheral physiological deterioration, such as altered cortical excitability and attention depletion (3, 9). If our hypothesis is confirmed, then mental fatigue will compromise motor and decision performance, as previously shown in sport-specific cognitive-motor protocols (2, 14).

The use of subjective measures, such as the FAS and the VAS, increases the ecological validity of the protocol. The FAS offers a multidimensional assessment of fatigue, covering physical and cognitive domains, and has demonstrated robust psychometric properties in clinical and non-clinical populations (32, 42). Its applicability in sport has been reinforced in recent validation efforts in Portuguese samples (42, 43). On the other hand, VAS is widely recognized for its sensitivity to immediate changes in perceived exertion and cognitive fatigue during highly demanding tasks (28, 29). Evidence also suggests that these subjective tools reliably reflect internal cognitive states, even in the absence of obvious physiological changes, thus offering complementary insights to neurophysiological and behavioral indicators (31, 33). By triangulating FAS, VAS, EEG, ETS, and performance outcome data, the protocol provides a multidimensional lens for examining the experiential and functional impacts of mental fatigue in football context.

The integration of EEG into this protocol is supported by recent evidence demonstrating that mental fatigue causes measurable changes in brain activity, particularly in oscillatory patterns linked to attention regulation and cognitive control. Notably, increased frontal theta power and decreased parietal alpha power have been repeatedly associated with sustained mental effort and attention decline (21, 48, 52). These neurophysiological signatures are especially evident during tasks that require prolonged executive engagement, such as those that mimic competitive sports conditions. Boord et al. (45) and Ke et al. (47) highlighted that mental fatigue leads to a reduction in task-specific cortical differentiation, impairing the brain's ability to maintain optimal states of attention. Di Rienzo et al. (50) and Gwon et al. (51) further demonstrated how EEG spectral analysis can sensitively capture the progressive onset of fatigue over time, even under motor imagery and dual-task conditions. Lum et al. (49) and Yang and Ren (23) suggested that EEG markers may vary depending on individual cognitive resilience and workload history, while Wascher et al. (19) provided initial experimental evidence linking increases in frontal theta to sustained attention overload. Furthermore, Rakhmatulin (17) reported EEG-based reductions in attention efficiency in mentally fatigued athletes, confirming the utility of EEG in sports contexts. These findings justify the inclusion of EEG in this protocol as a central tool for examining the cortical dynamics underlying mental fatigue and its relationship to impairments in visual and behavioral performance in football.

Importantly, although these oscillatory patterns are frequently observed under mental fatigue, they are not specific to fatigue alone and may reflect broader mechanisms related to attention regulation, motivational state, and cognitive workload. For this reason, the present protocol adopts a multimodal interpretative framework integrating EEG findings with behavioral, oculomotor, and subjective measures. Previous work has emphasized that alpha and theta oscillations are modulated by multiple cognitive and attentional processes and should not be interpreted as specific biomarkers of fatigue [e.g., (97, 98)]. Accordingly, in the present study, spectral changes are interpreted as context-dependent neurophysiological correlates rather than direct indicators of mental fatigue *per se*.

In this context, preserved behavioral performance accompanied by increased perceived effort or altered cortical oscillatory activity may be interpreted as short-term compensatory mechanisms aimed at sustaining task execution under mental fatigue. Such patterns can indicate increased cognitive resource allocation despite stable overt performance. Although the present protocol does not specifically model long-term compensatory adaptations, these mechanisms are acknowledged as relevant for future longitudinal investigation.

The inclusion of ETS is supported by growing evidence linking visual behavior to cognitive load and performance efficiency in sporting contexts. Mental fatigue has been shown to disrupt oculomotor dynamics, leading to longer fixation durations, fewer saccades, and altered pupillary responses, which are patterns associated with decreased attentional flexibility and compensatory cognitive effort (25, 26). In sport-specific contexts, ETS provides valuable insights into how athletes distribute visual attention during decision-making under pressure. For example, Zeuwts et al. (27) and Vansteenkiste et al. (54) demonstrated that more effective gaze strategies, characterized by shorter fixations and increased anticipatory saccadic movements, are associated with superior performance in passing and decision-making tasks in football. Crowe et al. (24) further highlighted how increased cognitive demands alter gaze fixation behavior, suggesting that visual metrics may sensitively reflect cognitive fatigue. Furthermore, Souto and Kerzel (53) emphasize the interdependence between selective visual attention and oculomotor control, underscoring the relevance of ETS measures in studies examining attentional resource allocation under fatigue. Collectively, these findings reinforce the utility of ETS for detecting subtle changes in visual search patterns that emerge from mental fatigue and affect performance.

The integration of sport-specific performance tasks into this protocol, namely the LSPT and the Y-SART, is based on their proven ability to assess technical execution and cognitive-motor integration under conditions of decision-making and physical demand. The LSPT has been widely validated to measure passing accuracy, decision-making, and technical skill in football, with proven reliability across different playing surfaces and age groups (34, 35). Le Moal et al. (56) further reinforces its ecological validity, highlighting its sensitivity to training status and competitive level in young players. Similarly, Y-SART provides a robust framework for assessing reactive agility and perceptual-motor responsiveness, essential attributes in football performance. Yuan et al. (2) demonstrated its effectiveness in capturing fatigue-induced declines in decision speed and movement accuracy, underscoring its value in mental fatigue paradigms. Trecroci et al. (36) also emphasized the test's discriminatory power between elite and sub-elite young players, supporting its relevance for talent identification and development profiling. Wang et al. (57) showed that reactive agility tests such as the Y-SART are particularly sensitive to cognitive load, with performance impairments linked to delays in stimulus processing and motor execution. Collectively, these two tests allow for the assessment of sport-relevant behaviors under ecologically valid and experimentally controlled conditions. When combined with ETS and EEG metrics, they allow for a nuanced understanding of how mental fatigue translates into tangible decreases in specific football actions, thereby increasing the applied value of the protocol for both research and practice.

The use of the ST as a method of inducing mental fatigue in this protocol is supported by a robust empirical basis that validates its effectiveness in overloading executive functions, namely inhibition and attentional control. The ST, by requiring constant resolution of conflicts between incongruent stimuli, intensely activates the anterior cingulate cortex, a region associated with conflict monitoring and cognitive effort (8). This sustained activation has been linked to reduced dopaminergic transmission, contributing to the subjective state of mental fatigue. Smith et al. (4) highlights that tasks such as the ST, due to their nature of inhibiting automatic responses, are particularly effective in inducing cognitive fatigue, making them suitable for experimental protocols that aim to simulate intense and prolonged mental demands.

In sporting contexts, Thompson et al. (5) observed that, despite its widespread use in studies on mental fatigue in football, the ST has limitations in terms of ecological validity, given that its repetitive and decontextualized structure differs from the complex cognitive demands experienced in real game situations. Nevertheless, its negative impact on physical and technical performance, as well as on decision-making, is well known, as evidenced by multiple studies. Marcora et al. (8), for example, demonstrated that after 90 min of a demanding cognitive task, participants showed a significant reduction in time to exhaustion during intense physical exercise, without relevant physiological changes, which reinforces the thesis that mental fatigue compromises physical performance mainly through an increase in the perception of effort. Thus, despite criticism regarding its contextual representativeness, the ST remains a reliable tool for experimental manipulation of mental fatigue, particularly in investigations that require strict control over the cognitive variables involved.

The statistical approach defined in this methodology and experimental protocol is structured to support the analysis of neurophysiological, visual, motor, and subjective outcomes using established quantitative methods. Descriptive statistics will characterize each variable, while paired and independent t-tests will assess intra- and intergroup differences before and after the intervention. A repeated measures ANOVA will be used to examine the effects of time and group interaction, with assumptions of normality and sphericity tested to ensure validity. Effect sizes (*η*^2^) and test power (π) will be reported to improve the interpretability and generalization of the results, following Marôco (90), Pallant (89), and Field (88). Pearson's correlation will be used to explore associations between domains (e.g., EEG activity and motor performance), interpreted according to Marôco (90). When appropriate, ANCOVA will control for individual variability, such as age or training experience. This analytical framework supports the protocol's goal of detecting the effects of mental fatigue on various dimensions of performance, based on robust methodological and statistical criteria.

